### Study design and procedures

This proposed study is a randomized controlled trial using a 4-group design including three intervention groups (physical training alone or cognitive training alone, or combined physical and cognitive training) and one waitlist control group. The study will comply with the principles of the Declaration of Helsinki 2013 and Good Clinical Practice Guidelines. Ethics approval was secured from the Human Subjects Ethics Sub-committee of the Hong Kong Polytechnic University-Department of Rehabilitation Sciences (HSEARS20170402001) and the Ethics Review Committee of the University of Santo Tomas-College of Rehabilitation Sciences (FI-2017-002). The SPIRIT guidelines were followed in the design of this study protocol.

Trained study personnel will interview the participants using questionnaires to obtain their demographic information and medical history, physical activity level and history of falls, and will conduct cognitive and physical performance tests to determine their eligibility to participate in this study. Only those who signed the informed consent will be included in this study.

Random allocation will be carried out by a third party not involved in the study by random draw to blindly allocate each participant to one of the four groups. To minimize experimental contamination through social interaction and communication among the participants, the interventions will be delivered at different sites.

Measurement points include baseline/pre-intervention, post-intervention, and six months follow-up assessments and will be conducted by trained study personnel blinded to the randomization assignment. Physiotherapists and occupational therapists who will be administering the interventions will not be involved in the outcome assessment. They will also have workshops and discussions to standardize the administration of the different training programs. After the intervention period, aside from a calendar-diary, monthly phone calls will also be done to follow up the participants about their fall status, physical activity, and exercise behavior. Figure 1 illustrates the study flow. Appendix shows the timeline of the study.

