### Interventions

#### Physical training alone (PT)

The participants in the PT group will be performing a series of physical exercises as a group supervised by trained physiotherapists. To ensure proper guidance and safety in the performance of the exercises, there will be one physiotherapist for every five participants.

The exercise program will start with 5–10 min of warm-up including calisthenics and general flexibility exercises, followed by 60–90 min of multicomponent exercise programme including endurance, strength and balance exercises (with a focus on balance training), and will end with 5–10 min of cool down including calisthenics and general flexibility exercises. This will be done three times per week over 12 weeks to achieve the recommended minimum accumulated 40 h of exercise [13]. The exercises will be progressed individually, increasing the repetitions or sets first before the resistance, to maintain a moderate level of exercise intensity which is 5 to 6 on a scale of 0 to10 for the level of physical exertion [47]. Rest periods will be provided whenever necessary. Table 1 shows the types of exercises included in this program.

**Table 1 Tab1:** Physical training program

Periods	Exercises	Progression
Warm-up (5–10 min)	Calisthenics and general flexibility	
Multicomponent exercise programme (60–90 min)	Walking over 10 m 1. Walking forward-backward, sideways 2. Turning figure of 8 walking 3. Tandem walking	10–12 rounds; 1–3 sets Increase step length and speed Over obstacles
	Sit-to-stand	8–12 repetitions; 1–3 sets Lower chair height
	Heel and toe raises	8–12 repetitions; 1–3 sets Hold or raise for longer
	Stepping in different directions	8–12 repetitions; 1–3 sets Longer or faster steps Step over obstacle
	Step-ups 1. Forward 2. 2. Lateral	8–12 repetitions; 1–3 sets Increase step height
	Graded reaching in standing 1. Table top - side to side, forward and diagonal reaching 2. Tapping markers on the wall 3. 3. Reaching down to chair, stool or floor	8–12 repetitions; 1–3 sets Narrower foot placement Increase distance to reach Standing on a softer surface (rubber mat) Stepping while reaching
Cool-down (5–10 min)	Calisthenics and general flexibility	

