#### Cognitive training alone (CT)

The participants in the CT group will be involved in a set of paper-based cognitive exercises as a group supervised by trained occupational therapists. To provide close monitoring and immediate feedback during the training, there will be one occupational therapist for every five participants.

The intervention will start with 5–10 min of warm up to give the instructions, followed by 60–90 min of cognitive training designed to train specific cognitive functions such as orientation, memory, attention and executive function, with emphasis on executive function which is associated with increased risk for falls in older adults [25], and will end with 5–10 min of cool down for feedback and processing of responses. This will be done once a week for 12 weeks which is the optimal duration of cognitive training [30]. Even though the cognitive training is delivered in a group, the difficulty level and progression will be individualized. Rest periods will be provided whenever necessary.

Table 2 shows the contents of the cognitive training. The contents of training for orientation and attention were based from Brum et al. (2009) [49], and Vojtkofsky and Feldman (2015) [50]. For memory, training will include rehearsal, association, visual imagery and concentration. The use of multiple strategies in memory training is chosen as larger improvement is expected with this approach compared to single strategy approaches [50, 51]. For executive function, training will consist of extensive repeated practice of practical tasks to simulate usual daily activities instead of relying on strategies to strengthen cognitive processes. This is founded on the process-based approach which has been proven to be highly effective in improving executive function [27].

**Table 2 Tab2:** Cognitive Training program

Periods	Components	Content
Warm-up (5–10 min)	Giving of instructions	
Cognitive training (60–90 min)	Orientation training	Orientation to person, place, and time with or without external cues like newspaper, calendar a. person – give full name, relatives, neighbors, age, occupation; name public officials b. place – provide address, location of islands/cities/provinces, favorite place/destination c. time – determine current time, day, month and year; schedule of TV shows; special occasions; weather, season

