#### Physical and cognitive training (PACT)

The participants in the PACT group will be performing activities that integrate cognitive training in physical exercise routines as a group supervised by trained personnel either physiotherapists or occupational therapists. To ensure proper guidance, safety, close monitoring and immediate feedback about their performance of the activities, every five participants will be supervised by one therapist.

The PACT programme will start with 5–10 min of warm-up including calisthenics and general flexibility exercises, followed by 60–90 min of exercises similar in design, intensity and progression with the PT group but with cognitive components incorporated in each type of exercise, and will end with 5–10 min of cool down including calisthenics and general flexibility exercises and a post-session discussion to recall the activities performed in the just-concluded session. This will also be done three times per week over 12 weeks. Rest periods will be provided whenever necessary. Table 3 presents the design of the PACT program. The participants will likewise be given the same brochures given to the PT and CT groups for additional information and reference.

**Table 3 Tab3:** Physical and cognitive training program

Periods	Exercises	Progression
Warm-up (5–10 min)	Calisthenics and general flexibility	
Multicomponent exercise programme (60–90 min)	Walking with executive function training • From a mixed set of objects (30 pieces) on a table at the start of the line, bring one object at a time walking over 10 m towards another table to sort the objects properly in 3–4 separate groups. Walking is done forward, backward, sideward, in figure of 8, or tandem.	10–12 rounds; 1–3 sets Increase step length and speed Walking over obstacles
	Sit-to-stand with orientation training • Stand every time to answer questions about orientation to person, place and time	8–12 repetitions; 1–3 sets Lower chair height
	Heel and toe raises with attention training • Follow visual cues to do heel or toe raises	8–12 repetitions; 1–3 sets Hold or raise for longer
	Stepping in different directions with memory training • Stepping on a set of specified number and sequence of markers on the floor	8–12 repetitions; 1–3 sets Longer or faster steps
	Step-ups with attention training • Follow verbal instructions on which foot to use to step-up	8–12 repetitions; 1–3 sets Increase step height

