#### Waitlist group (WG)

The participants in the WG will serve as the control group on waitlist. They will be instructed to go on with their usual daily routine and will receive the intervention, combined physical and cognitive training, at a later date.

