### Statistical analysis

Descriptive statistics will be used to summarize demographic data using mean standard deviations, and percentages. Baseline values across the groups will be compared using one-way ANOVA for interval/ratio data and Kruskal-Wallis test for nominal/ordinal data. The multivariate repeated measure ANOVA will be used to determine the pre- and post-intervention effects and differences among group data with a normal distribution; otherwise the Friedman test will be utilized. The incidence rate ratio, computed as the number of falls divided by the duration of falls monitoring for every participant, will be used to compare intergroup fall rate. An intention-to-treat analysis will be used for missing data due to dropouts. The *p*-value of < 0.05 is considered significant. Data analysis will be performed using SPSS version 23 for Windows.

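### PT, CT and PACT are delivered in therapist-led groups at different sites, but the sample size and the named analyses treat all participants as independent

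*Protocol article*

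**What the plan says.** All of this is in the protocol article.

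- **Allocation** (Study design and procedures): the unit is the individual, by "random draw to blindly allocate each participant to one of the four groups". The same section says, as a guard against contamination, that "the interventions will be delivered at different sites".
- **Delivery of PT**: participants will be "performing a series of physical exercises as a group supervised by trained physiotherapists", and "there will be one physiotherapist for every five participants".
- **Delivery of CT**: also in a group; "there will be one occupational therapist for every five participants".
- **Delivery of PACT**: also in a group; "every five participants will be supervised by one therapist".
- **Waitlist**: no sessions during the comparison period. "They will be instructed to go on with their usual daily routine".
- **Sample size computation**: effect size 0.39 (labelled Cohen's d), 80% power, 5% type I error and four groups give a total of 80, raised to 93 for dropout, with at least 23 per group. No design effect or ICC enters.
- **Statistical analysis**: "The multivariate repeated measure ANOVA will be used to determine the pre- and post-intervention effects and differences among group data" when the data are normal, the Friedman test otherwise, and an incidence rate ratio built from each participant's falls and monitoring time. No class, therapist or site term is named.

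**The concern.** People who train together share a therapist, a venue, peers and a session schedule, so their outcomes tend to be correlated even though they were randomised one by one. An analysis that treats them as independent uses too small an error term. The nominal 5% level and the confidence intervals are then not what they claim to be, and the error runs towards false positives. This bears on the trial's central hypothesis, that PACT is better than PT or CT alone, because both sides of each of those contrasts are group-delivered.

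A second issue follows from separating programmes by site. If a programme runs at one venue only, or as one class, a good or poor venue, therapist or group is indistinguishable from a good or poor programme, and no model can recover the difference. The stated 80% power allows for neither effect.

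**Working it through.** **1. The plan's own figure.** For a one-way ANOVA with four groups, the noncentrality is λ = f² × N, on 3 and N − 4 degrees of freedom.
- f = 0.385, N = 80: λ = 0.1482 × 80 = 11.86, power 0.81.
- f = 0.39, N = 80: λ = 0.1521 × 80 = 12.17, power 0.82. N = 76 already reaches 0.80.

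So 80 is reproduced within the rounding of 0.39 when that figure is read as f. A group-by-time interaction with two time points, correlation 0.5 and f = 0.19 also gives 80. Both routes assume independent participants.

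**2. Assumptions, because the article gives no values.** Class ICC 0.01, 0.02, 0.05 or 0.10. Classes of about five, taken from the staffing ratio: 23 per arm as 5 + 5 + 5 + 4 + 4. Venue variance share 0.01, 0.02 or 0.05 for the one-venue case. The waitlist is unclustered throughout.

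**3. Standard error, classes of five.** Design effect DE = 1 + (m − 1) × ICC with m = 5. The true standard error is √DE times the planned one.

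| ICC | DE | SE ratio |
|---|---|---|
| 0.01 | 1.04 | 1.02 |
| 0.02 | 1.08 | 1.04 |
| 0.05 | 1.20 | 1.10 |
| 0.10 | 1.40 | 1.18 |

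**4. Type I error of a nominal 5% test, classes of about five.** Simulated with no true effect and one normally distributed outcome: ordinary four-group ANOVA, and a two-sample t-test for PACT versus PT.

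| ICC | Four groups | PACT vs PT |
|---|---|---|
| 0.01 | 5.5–5.7% | 5.4% |
| 0.02 | 5.9% | 5.8% |
| 0.05 | 7.5% | 7.0% |
| 0.10 | 10.5% | 9.2% |

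Repeat runs agree to within about 0.3 percentage points. The normal approximation 2 × [1 − Φ(1.96/√DE)] for a pairwise contrast gives 5.5%, 5.9%, 7.4% and 9.8%. It is slightly higher at the upper end because two of the five simulated classes have four members.

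**5. Type I error if each programme has one venue.** Here m = 23, so DE = 1 + 22 × share.

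| Venue share | DE | Four groups | PACT vs PT |
|---|---|---|---|
| 0.01 | 1.22 | 8.2% | 7.5% |
| 0.02 | 1.44 | 12.2% | 10.5% |
| 0.05 | 2.10 | 23.6% | 18% |

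The four-group figures would be higher (about 9.5%, 14.6% and 30.4%) if the waitlist also had a shared venue effect, but it has no sessions.

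**6. Power.** Divide λ by DE = 1.20 (classes of five, ICC 0.05) at N = 80.
- f = 0.385: 11.86 / 1.20 = 9.88, power 0.73.
- f = 0.39: 12.17 / 1.20 = 10.14, power 0.74.

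This applies the design effect to all four arms, including the unclustered waitlist. It is therefore an upper bound on the loss at that ICC and class size.

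**The case against.** The strongest reply is that the size is unknown. No ICC is given, and with classes of five and an ICC of 0.01 the standard error is only about 2% too small. Workshops to standardise delivery and individual progression of the exercises plausibly keep therapist and class correlation low. All of that stands, and it limits the claim about magnitude. The simulated percentages are also for a continuous outcome, so they are not shown to hold for the primary outcome, the falls rate.

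Two stronger readings are tempting, and the article supports neither.
- A reader might infer that each programme has exactly one site, so that arm and site are wholly confounded. The article says only that sites differ between interventions. It calls the trial multicentre and does not give the number of sites per arm, so full aliasing is conditional.
- A reader might infer separate classes of five. One therapist per five is a staffing ratio, and a single class of about 23 with several therapists fits the text equally well. That would worsen the clustering and also make a class effect inseparable from arm.

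Nor should site be read as a baseline population difference. Allocation is individual, so recruitment community is balanced in expectation. What is mixed in is an effect of delivery, and adjusting for recruitment community would not remove it.

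It can also be said that random-effect structure belongs in an analysis plan not shown here, and that site separation is a deliberate guard against contamination. The second point is fair, and the fix leaves that choice alone. The first holds only in part. The article itself fixes the group delivery, the sample size and the tests, and followed as written those tests assume independence.

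**Conclusion.** The point holds in conditional form. Individual randomisation followed by group delivery in three arms, analysed as if participants were independent, understates standard errors for any positive within-class or within-therapist correlation. How much depends on assumed values. The inflation is negligible at an ICC of 0.01 in classes of five and reaches about 9% to 10.5% false positives at 0.10. It is larger if each programme has one venue: about 7.5% to 18% for PACT versus PT over venue shares of 0.01 to 0.05. The stated 80% power is a no-clustering figure; at an ICC of 0.05 in classes of five it would fall to no lower than about 0.73 to 0.74. The structural conclusion is firm. The numbers are illustrations for a continuous outcome.

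**What to change.** 1. Record class, therapist and venue identifiers for every participant in PT, CT and PACT, and state the number of classes and venues per arm.
2. In Statistical analysis, specify a partially nested model for the falls count and for the continuous outcomes: a random effect for class or therapist in the three training arms, each waitlist participant as a singleton, and a small-sample correction. Classes of about five would give only some five clusters per arm, so the variance component will be imprecise.
3. In Sample size computation, say that the power figure assumes no clustering.
4. If a programme has a single venue or a single class, so that the term cannot be separated from arm, state that the contrasts compare programme-plus-venue packages. Report how the conclusions change over a range of assumed ICCs.

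Delivery need not change. The mixed and generalised mixed procedures in SPSS 23, the package already named, can fit such models. The cost is some extra record-keeping, new analysis wording, somewhat wider intervals and a slightly less favourable power figure.

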**Fig. 1 Fig1:**
[figure not shown]
Flow diagram of the study

### Sample size computation

The sample size and power calculations will be based on fall rate which is the primary outcome of the study. Using statistical software Gpower 3.1.9.2, a priori power analysis was conducted using the computed effect size (Cohen’s d = .39) from Trombetti et al. (2011) [46]. Assuming 80% power with 5% Type 1 error and four groups, the calculated total sample size is 80. Considering a 16% dropout rate (Trombetti et al., 2011) [46], the total number of participants is inflated to 93. There should be at least 23 participants per group.

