On the contrary, a study that combined resistance training and cognitive training in older adults with MCI concluded that doing high-intensity resistive training alone for six months lead to significant increase in global cognitive function, memory and executive function while participating in combined training unexpectedly and significantly reduced the benefits of isolated progressive resistance training on executive and global cognitive function [39]. In another study also involving older persons with MCI, dual modality cognitive-physical training and single modality interventions of cognitive training alone or physical exercise alone resulted in no significant differences in cognitive outcome measures [40]. In a systematic review, both older adults with and without cognitive impairment gained improvements in cognitive functions and functional status from combined physical exercise and cognitive training interventions [41]. However, the evidence is lacking to ascertain the superiority of combined interventions when compared to active control groups. More studies with good methodological quality are warranted to explore the potential benefits of this new treatment approach [41].

The link connecting the improvements in cognitive function and physical factors after undergoing physical exercise and cognitive training, singly delivered or in combination, to the reduction of falls and the decrease in falls risk in the geriatric population, particularly to those with MCI, is yet to be established.

Thus, this study primarily aims to determine the effectiveness of combined physical and cognitive training on preventing falls and reducing the risk of falls among community-dwelling older adults with MCI. The hypothesis is that an intervention that incorporates elements of both physical exercise and cognitive training in one treatment program is more effective compared to physical exercise or cognitive training alone in preventing the occurrence of falls and in decreasing the risk of falls in older adults with MCI living in the community.

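### Cohen's d of 0.39 with 80 participants does not give 80% power for the fall-rate comparison; on a single-value comparison it gives about 15–27% for the four-group test and about 23% pairwise

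*Protocol article*

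**What the plan says.** The protocol article, Sample size computation, ties the calculation to the primary outcome: "The sample size and power calculations will be based on fall rate which is the primary outcome of the study". The tool is given ("Using statistical software Gpower 3.1.9.2") and so is the effect: "a priori power analysis was conducted using the computed effect size (Cohen’s d = .39". The result follows: "Assuming 80% power with 5% Type 1 error and four groups, the calculated total sample size is 80". For dropout, "the total number of participants is inflated to 93", and "There should be at least 23 participants per group". The section names no test family, number of measurements, correlation or conversion of the effect size.

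Under Statistical analysis, falls are handled through a quantity "computed as the number of falls divided by the duration of falls monitoring for every participant, will be used to compare intergroup fall rate". That is one value per participant, compared between groups.

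The hypothesis, at the end of the Background, is pairwise: the combined programme "is more effective compared to physical exercise or cognitive training alone in preventing the occurrence of falls".

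**The concern.** Cohen's d is a standardised difference between two groups. A four-group F test is sized on Cohen's f, the standard deviation of the group means divided by the within-group standard deviation. If d is the largest gap between groups, f is at most d/2. A total of 80 for an effect of 0.39 is therefore far too small if 0.39 really is d and one value per participant is compared.

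The 80% power claim for the primary outcome is at stake. The Abstract projects a significantly lower falls rate with the combined programme than with single or no intervention. At roughly 23% power per contrast, a non-significant result is the more likely outcome even if the planning effect is real. A reader who relies on the stated 80% would give that result too much weight.

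**Working it through.** **Inputs from Sample size computation:** effect 0.39 (labelled d), alpha 0.05, power 0.80, k = 4 groups, N = 80 before dropout, 93 after. **Assumptions:** equal groups (20 per arm at N = 80), two-sided t-tests, and d as the largest gap among the four means.

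**Step 1. The plan's own figure.** One-way F test with 3 and N − 4 degrees of freedom and noncentrality λ = N·f².
- Entering f = 0.390 gives a smallest balanced N of 76 (power 80.2%). At N = 80, λ = 80 × 0.39² = 12.17 and power is 82.5%.
- N = 80 is the smallest balanced total for f from 0.379 to 0.389. Values of 0.385–0.389 print as 0.39.

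**Step 2. A second route to the same total.** For a group-by-time interaction with m measurements and correlation ρ, λ = N·f²·m/(1 − ρ). With f = 0.39/2 = 0.195, m = 2, ρ = 0.5 and N = 80, λ = 80 × 0.195² × 2/0.5 = 12.17. This equals Step 1 with the same degrees of freedom, so N is again 76, with 82.5% power at 80. With ρ = 0.48, N is 80 (80.8%). The printed total cannot tell the two routes apart.

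**Step 3. From d = 0.39 to f for four equal groups.**
- Two arms at each extreme (most favourable): f = d/2 = 0.195.
- One arm differs from the other three: f = d·√(3/16) = 0.169.
- One arm at each extreme, two midway (least favourable): f = d·√(1/8) = 0.138.

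**Step 4. Power of the four-group test for one value per participant.**

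| f | λ at N = 80 | Power, N = 80 | Power, N = 93 | Total for 80% |
|---|---|---|---|---|
| 0.195 | 3.04 | 26.5% | 30.7% | 292 |
| 0.169 | 2.28 | 20.6% | 23.6% | 388 |
| 0.138 | 1.52 | 14.9% | 16.8% | 580 |

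**Step 5. The hypothesised pairwise contrasts.** Two-sample t-test, noncentrality d·√(n/2).
- n = 20 per arm: 0.39 × √10 = 1.23 on 38 degrees of freedom, power 22.5%.
- n = 23 per arm: power 25.3%.
- Power of 80% for one unadjusted contrast needs 105 per arm, or 4 × 105 = 420 over four arms.

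**Step 6. What 80 evaluable participants can detect with 80% power.** For the four-group test, f of about 0.38 (0.39 gives 82.5%). For one pairwise contrast at 20 per arm, d of about 0.91.

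**The case against.** The strongest reply is that the calculation may have been done correctly for a different model. Outcomes measures says that primary and secondary outcomes are taken at baseline, after the intervention and six months later. Falls history is collected before randomisation, and Statistical analysis names a multivariate repeated-measures ANOVA for pre- and post-intervention effects. Step 2 shows that a properly halved effect in such a model gives 76–80.

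This stands as far as cause is concerned. A reader might infer that the authors must have typed d into the field for f, or that 80 can arise in no other way. The article supports neither statement: it names no test, and the software settings may be in a fuller document that is not shown. The d-as-f explanation is an inference.

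It does not rescue the power claim. The sample size is stated to rest on fall rate, and the fall-rate analysis uses one rate per participant over the monitored period. No diary monitoring before randomisation is described; the earlier falls history is an interview item. The route also needs the most favourable pattern of means: with ρ = 0.5 and two measurements, power at 80 falls to 69% for f = 0.169 and 50% for f = 0.138.

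A second reply is that falls are to be compared by a rate ratio, so neither the F test nor the t-test is the exact analysis. That is fair, and it makes the percentages conditional. But a standardised difference is the scale the plan itself chose, and power on a count scale would need fall rates and dispersion that the article does not give.

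**Conclusion.** The point holds for the stated primary outcome. With d = 0.39 as the largest gap between groups and a single value per participant, 80 evaluable participants give about 15–27% power for the four-group test (17–31% if all 93 are analysed) and about 23% for each of the two hypothesised contrasts. The printed effect size, power, number of groups and total cannot all be right for that comparison.

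The size rests on equal allocation, 5% two-sided testing without multiplicity adjustment, and a normal-theory approximation to the fall-rate comparison. It would be too strong to call 15–27% the trial's power without those conditions. How the total of 80 was reached cannot be settled from the article.

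**What to change.** In Sample size computation:

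1. State the test family, any conversion from d to f, and any repeated-measures assumptions (number of measurements, correlation).
2. Replace the 80% power claim for fall rate. With 80 evaluable participants, 80% power holds only for f of about 0.38–0.39, or a pairwise d of about 0.9. For d = 0.39, power is at most about 27% for the four-group comparison and about 23% for combined versus physical or combined versus cognitive training.
3. If the total came from a repeated-measures calculation, say so, and say that it does not describe the power of the fall-rate comparison.

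Enrolment does not change. The cost is protocol wording and a less favourable power statement.

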**Discussion:**

Considering the possible physical, social, financial and psychological consequences of a fall, we hope to provide insights on the effectiveness of combining physical and cognitive training on falls and fall-related factors for older adults with MCI. It is projected that the combined interventions will lead to significantly lower falls rate and reduced risk of falls compared to using single or no intervention.

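### The 80% power at N = 80 fits an overall four-group test and is not shown for the trial's hypothesis that combined training beats each single programme

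*Protocol article*

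**What the plan says.** Under Sample size computation, the protocol article ties the calculation to the primary outcome: "The sample size and power calculations will be based on fall rate which is the primary outcome of the study". The effect size comes from an earlier trial: "a priori power analysis was conducted using the computed effect size (Cohen’s d = .39". The result is "Assuming 80% power with 5% Type 1 error and four groups, the calculated total sample size is 80". After a 16% dropout allowance "the total number of participants is inflated to 93", and "There should be at least 23 participants per group". The section names neither the test nor the comparison, and gives no expected values for the four arms.

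The hypothesis closes the Background, under Combined physical and cognitive training. It says that a programme with both elements "is more effective compared to physical exercise or cognitive training alone in preventing the occurrence of falls". The Discussion paragraph of the Abstract projects that "the combined interventions will lead to significantly lower falls rate and reduced risk of falls compared to using single or no intervention".

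Under Statistical analysis, fall rates are to be compared between groups by incidence rate ratio, and a p-value "of < 0.05 is considered significant". No rule says which comparisons must succeed for the hypothesis to be supported.

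**The concern.** An overall four-group test asks whether any arm differs from any other. The hypothesis asks whether PACT is better than two particular arms. The questions can have different answers: if all three programmes worked equally well and only the waitlist group (WG) did worse, the overall test would often be significant although the hypothesis was false.

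The risk lies in how the results are read. A non-significant PACT vs PT or PACT vs CT result could be taken as evidence against combining the programmes, because the trial is described as having 80% power. A significant overall result, or PACT vs waitlist alone, could be taken as support for the combination.

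**Working it through.** **Inputs.** From Sample size computation: effect size 0.39, power 80%, type 1 error 5%, four groups, N = 80 (20 per group), at least 23 recruited per group. From the Background: the contrasts PACT vs PT and PACT vs CT. Assumed because the article does not give them: two-sided 5% tests without multiplicity adjustment, a normal outcome with common SD (the framework of the sizing itself), and the pattern of arm means, for which a range is shown.

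**Step 1: reproduce N = 80.** For a one-way four-group F test, the noncentrality is λ = N·f², with 3 and N − 4 degrees of freedom.

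- With f = 0.39 and N = 80, λ = 80 × 0.1521 = 12.17 and power is 82.5%.
- With N = 76, power is 80.2%, so exactly 0.39 needs only 76.
- An unrounded f of 0.385 to 0.389, which prints as .39, falls just short at 76 (79.0% to 79.96%) and needs 80 in equal groups.

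The other variants tried do not give 80. As a d between two means, 0.39 needs 104 per arm. Converted from d to f (0.195 or less), it needs 292 or more in total. Repeated-measures between-group tests at 0.39 need 52 to 60, and interaction tests at 0.195 need 64 to 76.

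**Step 2: translate f = 0.39 into gaps between arms.** f is the SD of the four arm means in units of the within-group SD. Each pattern is scaled so that this SD is 0.39.

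- Only PACT differs, pattern (0, 0, 0, 1): SD 0.433, so the gap is 0.39 / 0.433 = 0.90 SD.
- PT and CT have half the PACT benefit, pattern (0, ½, ½, 1): SD 0.354, so the full range is 0.39 / 0.354 = 1.10 SD and the gap is 0.55 SD.
- WG < CT < PT < PACT equally spaced: SD 0.373, so the full range is 1.05 SD, with gaps of 0.35 SD to PT and 0.70 SD to CT.

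Because λ depends only on f and N, overall power is 82.5% in every pattern at 20 per arm.

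**Step 3: power for the contrasts.** Simulated with pooled-variance t contrasts, 20 per arm, 76 degrees of freedom:

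| Pattern | PACT beats PT | PACT beats both PT and CT | Overall test |
|---|---|---|---|
| Only PACT differs | 80% | 69% | 82.5% |
| PT and CT have half the benefit | 41% | 25% | 82.5% |
| Equally spaced | 19% | 17% | 82.5% |
| Only WG differs | 2.5% | 0.5% | 82.5% |

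**Step 4: detectable gap.** If PACT is better than every other arm by the same amount, 0.90 SD gives 80% on one contrast and 69% on both. A gap of 1.00 SD gives 88% and 80%.

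**Step 5: sensitivity.**

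- All 23 per arm analysed: 77% for both contrasts if only PACT differs, 29% under half benefit.
- Beating either single programme suffices, 20 per arm: about 91% and 56%.
- One-sided 5% tests, 20 per arm: about 80% and 37% for both contrasts.
- 0.39 taken literally as a d for PACT against each other arm: 23% per contrast, 11% for both.

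**The case against.** Several objections have force.

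- **The test is inferred.** The article does not name it, and exactly 0.39 gives 76, not 80. The inference is still the best available, because no other variant tried comes out at 80.
- **No success rule requires both contrasts.** The Background uses the word *or*, and Statistical analysis sets no rule. Reading the hypothesis as both is reasonable, and the Abstract's projection against single or no intervention leans that way, but it remains an assumption. Under the weaker reading the best-case power exceeds 80%; the half-benefit case still falls short.
- **The patterns are not in the article.** The 25% illustrates one plausible pattern and is not a property of the trial. The Background does describe exercise alone as effective against falls in older adults generally and promising in cognitive impairment, so a pattern in which PT does nothing is not the obvious one to plan on.
- **The scale differs.** The sizing uses a standardized mean difference, whereas the planned comparison is an incidence rate ratio. Gaps in SD units do not describe the power of that analysis.

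A reader might infer that 69% is a ceiling, or that power always falls at least 11 points short of 80%. The documents do not support either. With the overall effect held at 0.39, joint power reaches about 75% if the waitlist arm does better than PT and CT, 77% if only PACT works and all 23 per arm are analysed, and 82% with both. Those are favourable conditions, but nothing in the article excludes them.

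Detailed reporting rules for the contrasts may stand in an analysis plan that is not shown. The published power statement is fixed in this article, however, and that is where the mismatch lies.

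**Conclusion.** The concern holds in a limited form. The printed 80% is not shown to be the power for the trial's own question, and under plausible patterns it is not that power. It can be reproduced, approximately, only as power for an overall four-group test, which keeps its 82.5% even where the hypothesis is false.

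The size of the gap depends on conditions the article does not settle: whether both contrasts are needed, how many per arm are analysed, whether tests are two-sided, and how well PT and CT work. With both contrasts, 20 per arm and two-sided 5% tests, joint power is about 69% if only PACT works, 25% under half benefit and 17% under equal spacing. These figures accept 0.39 as an f, which is generous. If it is a d, as labelled, and is the largest gap between arms, f is about 0.14 to 0.20 and even the overall test has only about 15% to 27% power at N = 80.

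**What to change.** In Sample size computation:

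1. Do not present 80% as power for the PACT hypothesis. State which test it refers to and whether the effect size is a d or an f, after reconciling the Cohen's d label with the calculation. Until that is done, the section should not affirm that 80% holds for the overall test either.
2. Add the power or detectable difference for PACT vs PT and for PACT vs CT at the planned number per arm, on the scale of the falls-rate comparison. On the sizing's own standardized scale, the values at 20 per arm are about 0.90 SD for 80% on one contrast and about 1.0 SD for both.
3. Say whether the hypothesis needs both contrasts.

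In Statistical analysis, state that an overall four-group result, or PACT vs waitlist alone, does not support the hypothesis, and that both contrasts will be reported with confidence intervals.

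The cost is wording in two sections and one recalculation. Enrolment is unchanged, and the downside is a less favourable stated power. Raising joint power to 80% would be a separate design decision: on the standardized scale it would take about 25 evaluable per arm (100 in total) if only PACT works, and about 65 per arm (260 in total) under half benefit.
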